#### Cost of hospitalization

3.2.4

Hospitalization expenses from admission to discharge from the ICU will be recorded.

### Safety assessment

3.3

Vital signs; blood, urine, routine stool, liver, and kidney function test findings; and electrocardiogram will be recorded daily for the entire study duration. And any AEs observed will be documented in detail.

### Compliance

3.4

The researchers will pay close attention to patients’ compliance and exclude patients with poor compliance. The researchers will also pay attention to the daily vital signs and relevant safety indicators of each patient and immediately assess whether they can continue to participate in the study if AEs related to the intervention measures or other disease conditions arise, and take effective intervention measures for any adverse reactions.

### Adverse events

3.5

Any AE that occurs during the clinical study, whether or not it has a causal relationship with the experimental intervention, will be regarded as an AE. The AE report form will be completed. The occurrence time, severity, duration, measures, and results of AEs will be recorded. If any serious AEs occur, they will be reported to the local Adverse Drug Reaction testing center and ethics committee within 24 hours.

### Data management and quality control

3.6

Before initiating the trial, all researchers will be required to attend a series of mandatory training courses to ensure that they fully understand the study protocol and treatment standards and ensure the accuracy and integrity of the clinical treatment and trial data recording. The research leader will monitor the progress of the study regularly. The data observer will first record all data in the paper version of the CRF and then double input the data into the electronic data acquisition system. The test supervisor will regularly check the progress of the study and the completeness and compliance of the CRF records. To ensure data objectivity, the data observers and statisticians will not know the group allocations of the patients. An independent quality inspector will monitor the entire study process.

### Statistical analysis

3.7

Before analysis, the data of 2 participants with complete data will be carefully checked to ensure the accuracy of the data. All data will be analyzed by intention. SPSS version 22.0 (Chicago, IL) will be used to analyze the data. The measurement data will be represented as mean ± standard deviation. The paired t-test will be used to perform the before and after analyses of the same group. The chi-square test will be used for the counting data and the rank sum test will be used for grade data. The Kaplan–Meier method will be used for univariate analysis to explore each possible related factor. The multivariate Cox model will be used to adjust for variables with statistical significance (*P* < .05) in univariate analysis to detect the influence of these variables on the study measure outcomes.

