### Sample size

2.4

According to the preliminary clinical research data, the total effective rate of “improved sitting Wuqinxi” in preventing and treating common complications and adverse outcomes in mechanically ventilated patients was statistically different between the groups. The test level was α = 0.05. The test efficiency was 1 - β = 0.80. The sample size was estimated using G∗Power (version 3.1.2, Franz faul, Universitat kiwl, Germany), and the effect size was set as d = 0.50. After calculation, the number of participants needed in each group was 64, totaling to 128 participants. Considering an attrition rate of ≤20%, the total number of participants required for this study was calculated to be 160, with 80 participants in each group.

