### Randomization and allocation concealment

2.5

Members of the Sichuan Traditional Chinese Medicine Evidence-Based Medicine center will use SAS 9.2 software (SAS, Cary, NC) to generate 160 random serial numbers. After screening and baseline evaluation, mechanically ventilated ICU patients will be randomly divided into the experimental and control groups in a 1:1 ratio. The group allocation number will be provided in a continuously numbered sealed envelope of carbon-free paper. The envelope will be kept by the research administrator, who will not be directly involved in the recruitment or follow-up of any participants, and their group allocation number will be disclosed later. The administrator will open the envelopes and provide participants with their group allocation number on the day of inclusion. The distribution of patients in each experimental center is shown in Table 1.

**Table 1 T1:** Distribution of patients in each trial center.

Number of each center	Name of each center	Experimental group (patients)	Control group (patients)
01	Affiliated Hospital of Chengdu University of traditional Chinese Medicine	40	40
02	Leshan Hospital of traditional Chinese Medicine	20	20
03	Affiliated Hospital of Chengdu University	20	20
Total		80	80

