#### Exclusion criteria

2.7.2

The following patients will be excluded:

(1)Patients with rapidly progressive neuromuscular diseases(2)Patients with Acute Physiology and Chronic Health Evaluation II score >30 and expected to die within 48 hours(3)Patients with increased intracranial pressure, limb disability or loss, and unstable fracture(4)Patients included in other clinical trials

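### Severity adjustment is absent for complications and graded outcomes and data-dependent for time outcomes; pre-specifying baseline APACHE II as a covariate could recover precision

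*Protocol article*

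**What the plan says.** All references are to the protocol article.

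- **2.7.2 Exclusion criteria.** The severity score appears here and nowhere else in the shown text: "Patients with Acute Physiology and Chronic Health Evaluation II score >30 and expected to die within 48 hours".
- **2.5 Randomization and allocation concealment.** "After screening and baseline evaluation, mechanically ventilated ICU patients will be randomly divided into the experimental and control groups in a 1:1 ratio". Table 1 fixes equal arm totals within each centre. No severity factor is described.
- **3.7 Statistical analysis.** For counts and grades: "The chi-square test will be used for the counting data and the rank sum test will be used for grade data". For measurement data the only test named is a paired t-test within each group. Kaplan–Meier analysis then screens candidate factors one at a time, and those with P < .05 go into a multivariate Cox model. The stated purpose of that model is to show how those variables affect the outcomes.
- **3.2 Observation index.** The outcomes are complications, ventilation time, length of ICU stay and cost.
- **2.4 Sample size.** "The test level was α = 0.05"; "The test efficiency was 1 - β = 0.80"; "the effect size was set as d = 0.50"; and "the number of participants needed in each group was 64, totaling to 128 participants", raised to 160 for attrition of up to 20%.

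**The concern.** Sections 2.6 and 2.7.1 admit acute exacerbations of COPD, ARDS from mild to severe, and postoperative respiratory failure. Because exclusion 2 joins its two conditions with 'and', scores above 30 can also enter. Severity at entry can reasonably be expected to relate to complications, ventilation time, ICU stay and cost.

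Where a baseline variable predicts the outcome, leaving it out of the comparison keeps its share of the variance in the error term and so costs power. The plan aims for 80% power after allowing for attrition, so there is little to spare.

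The Cox step only partly meets this need. It suits time-to-event outcomes, not the counts and grades given to chi-square and rank sum. Whether severity enters the model depends on a significance test in the trial's own data, so the adjusted comparison is not fixed in advance.

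**Working it through.** **1. The plan's own figure.** Inputs from 2.4: α = 0.05 (sidedness not stated), power 0.80, d = 0.50. A two-sided two-sample t-test (noncentral t) needs 63.77 per arm, so 64 per arm and 128 in total. Power at 64 per arm is 0.8015, or 80.1%. A one-sided test would need only about 50 per arm (normal approximation), so the two-sided reading is the one that fits. Attrition: 128 / (1 − 0.20) = 160. The stated 64, 128 and 160 all reproduce, so the sample size is not in error.

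**2. Effect of adjusting for one baseline covariate, continuous outcome.** If the score has correlation ρ with the outcome, the residual SD becomes √(1 − ρ²) and the effective standardised difference is 0.50 / √(1 − ρ²). The document gives no ρ, so a range is assumed.

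| ρ (assumed) | residual variance, 1 − ρ² | power at 64 per arm | n per arm for 80% power |
|---|---|---|---|
| unadjusted | 1.00 | 80.1% | 64 |
| 0.1 | 0.99 | 80.5% | 64 |
| 0.2 | 0.96 | 81.7% | 62 |
| 0.3 | 0.91 | 83.7% | 59 |
| 0.4 | 0.84 | 86.5% | 54 |
| 0.5 | 0.75 | 90.0% | 49 |

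The gain is under 2 points up to ρ = 0.2 and about 4 to 10 points for ρ from 0.3 to 0.5. The formula is for a linear model of a continuous outcome. For logistic, ordinal or Cox models it is indicative only.

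**3. Chance imbalance.** With 80 per arm, the standard error of the difference in mean standardised score is √(2/80) = 0.158. The probability of an imbalance of at least 0.3 SD in either direction is 2 × P(Z > 0.3/0.158) = 5.8%.

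Given an imbalance of exactly 0.3 SD and no treatment effect, the unadjusted z statistic is centred at ρ × 0.3 / 0.158 with SD √(1 − ρ²).

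- ρ = 0.3: centre 0.569, SD 0.954; rejection rate 7.6%.
- ρ = 0.5: centre 0.949, SD 0.866; rejection rate 12.2%.

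These rates are conditional on that imbalance. Averaged over all randomisations, the rate is 5%.

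**4. Which outcomes the stated analysis can adjust.**

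| Outcome type | Test in 3.7 | Severity adjustment |
|---|---|---|
| Complications (counts) | chi-square | none |
| Graded data | rank sum | none |
| Ventilation time, ICU stay | Kaplan–Meier, then Cox | only if severity is among the factors screened and reaches P < .05 |
| Cost (measurement data) | no between-arm test named | none stated |

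**The case against.** Four objections carry weight.

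- **The plan does adjust.** A reader who stops at the chi-square sentence might infer that no adjustment is planned. Section 3.7 does include a Cox model, and APACHE II is not barred from the factors screened. This stands for ventilation time and ICU stay. It does not help complications or graded data, and selection by P < .05 leaves the adjustment undecided until the data are in.
- **The score may not exist for everyone.** A reader might infer that exclusion 2 forces a score on all 160 patients. Its wording needs both conditions, so a patient not expected to die within 48 hours could be cleared without one. Figure 2, the data-collection schedule, is not shown. Availability cannot be assumed, and the fix has to ask for the score.
- **Covariates are often named in a separate analysis plan.** True, and such a plan may name APACHE II. However, the article itself fixes the tests and the selection rule, and those choices can be judged as written.
- **The size is assumed and fits only part of the plan.** This also stands. No correlation is given, and the power figures are for a between-arm comparison of a continuous outcome, which 3.7 does not name. Section 2.7.1 also requires clear consciousness and stable cardiopulmonary function, which may narrow the severity range and so weaken the correlation.

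**Conclusion.** The point holds as a recommendation on efficiency and pre-specification. It is not an error in a stated figure. In the shown text, complications and graded outcomes get no severity adjustment, and time outcomes get it only if a data-driven screen selects it.

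For a continuous outcome the possible gain is about 1.6 to 10 power points at assumed correlations of 0.2 to 0.5, and close to nothing at 0.1. No size is established for the binary, graded or time-to-event outcomes.

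A reader might infer from the 7.6% and 12.2% figures that the unadjusted tests inflate the false-positive rate. They do not: randomisation keeps the unconditional type I error at 5%. An imbalance matters only for interpreting a trial in which it has occurred, and one of 0.3 SD or more would occur in 5.8% of trials with 80 per arm.

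**What to change.** In 3.7, name baseline APACHE II as a continuous covariate in every between-arm model, in place of selection by univariate P < .05. State that it is recorded at screening for all randomised patients. The models would be:

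- complications: logistic regression, reported with a standardised risk difference;
- graded data: ordinal regression;
- ventilation time and ICU stay: the Cox model already planned, with treatment arm and APACHE II as fixed terms and a stated way of handling death and censoring;
- cost: a linear model for log cost.

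Keep the unadjusted chi-square and rank sum tests as sensitivity analyses.

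The cost is analysis wording and one more model term, plus one baseline item if the score is not already collected for everyone. No extra patients are needed. The downside is small: little is gained if severity predicts the outcome weakly.

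### Section 3.7 makes Kaplan–Meier the univariate method for every candidate factor; any continuous factor must then be grouped, which costs power in the screen that selects the Cox covariates.

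*Protocol article*

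**What the plan says.** Section 3.7 (Statistical analysis) of the protocol article describes two linked steps. The first is univariate: "The Kaplan–Meier method will be used for univariate analysis to explore each possible related factor". The second is multivariable: "The multivariate Cox model will be used to adjust for variables with statistical significance", with significance defined as P < .05 in the univariate step. The stated aim is to learn how those variables influence the outcomes.

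No other univariate time-to-event method is named, and the first sentence makes no exception for continuous variables. The same section expects continuous data, since it summarises measurement data by mean and standard deviation. The article does not list the candidate factors.

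**The concern.** Kaplan–Meier estimates one survival curve per group, and the test that goes with it compares groups. It does not take a covariate measured on a continuous scale. Applied to every factor, the sentence therefore requires each continuous candidate to be grouped before it can be screened.

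This matters because the screen acts as a gate. A real prognostic factor that falls short of P < .05 because it was coarsened does not enter the Cox model. It is then missing both from the adjusted treatment comparison and from the reported set of related factors. The problem is separate from whether a P < .05 screen should be used at all: with the screen kept, a univariable Cox model would still avoid the loss.

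**Working it through.** **1. The plan's own figures.** Section 2.4 gives: "The test level was α = 0.05"; "The test efficiency was 1 - β = 0.80"; "the effect size was set as d = 0.50". For a two-sided two-sample t-test, the normal approximation is n = 2(1.96 + 0.8416)² / 0.50² = 62.8, so 63 per group. The noncentral t gives 63.77, so 64. This agrees with "the number of participants needed in each group was 64, totaling to 128 participants". For attrition, 128 / (1 − 0.20) = 160, as stated: "Considering an attrition rate of ≤20%, the total number of participants required for this study was calculated to be 160". The sample size reproduces and does not depend on the factor screen. It supplies the two sizes used below, N = 160 (all patients) and N = 128 (after 20% attrition).

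**2. Information lost by a median split.** For a normal covariate, the squared correlation between the variable and its median-split indicator is 2/π = 0.64. About 36% of the information is lost. For screening one factor, 160 patients with a median split are worth about 160 × 0.637 = 102 patients with the factor kept continuous.

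**3. Approximate power.** The documents give no factor effect, so log hazard ratios of 0.20, 0.25 and 0.30 per SD are assumed (hazard ratios 1.22, 1.28 and 1.35). With D events and unit variance:

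- continuous: power ≈ Φ(β√D − 1.96)
- median split: power ≈ Φ(β√(D × 2/π) − 1.96)

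With D = 160, √D = 12.65. At β = 0.25 the continuous form gives Φ(3.162 − 1.96) = Φ(1.202) = 88.5%. The median split gives Φ(2.523 − 1.96) = Φ(0.563) = 71.3%.

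**4. Simulation.** Exponential event times, one standard-normal factor, two-sided 0.05, 3,000 replicates per setting (Monte Carlo standard error at most √(0.25/3000) = 0.9 points). The Cox score test on the continuous factor was compared with the log-rank test after grouping.

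| Setting | Analysis | log HR 0.20 | 0.25 | 0.30 |
|---|---|---|---|---|
| N = 160, no censoring | continuous | 70% | 86% | 95% |
| | median cut | 50% | 68% | 83% |
| | 80th-percentile cut | 44% | 61% | 76% |
| N = 128, 20% censored (rate set at no effect) | continuous | 52% | 67% | 84% |
| | median cut | 35% | 49% | 65% |

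Across N = 128 or 160 and 0% or 20% censoring, the median cut costs about 13 to 20 points. The approximation in step 3 gives slightly higher power but a similar gap at β = 0.25 (17 points, against 18 simulated).

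**5. False positives when the factor has no effect.** Over the same four combinations of size and censoring, the rejection rate is about 5% with the factor continuous, about 5 to 6% with one fixed cut (median or 80th percentile), and 32 to 34% when the best of 17 cuts between the 10th and 90th percentiles is kept.

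**The case against.** The strongest reply is that the article names no continuous candidate. Age appears only as an inclusion criterion. The severity score appears only in an exclusion rule: "Patients with Acute Physiology and Chronic Health Evaluation II score >30 and expected to die within 48 hours". Liver and kidney tests are monitoring items in the Figure 2 legend and section 3.3. Several natural candidates are categorical, such as arm, centre, diagnostic group and ARDS grade, and for these Kaplan–Meier is suitable. That stands as a limit on the examples. It does not remove the point, because the sentence covers every factor and leaves no route for a continuous one.

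A second reply is that a factor list, its coding and any cut-points are details that a condensed article may leave to the full protocol or analysis plan. That also stands: missing cut-points are not a finding here. But a fuller document that followed this sentence could only supply cut-points; it would still have to categorise.

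Three stronger readings are tempting and are not supported:

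- **That the plan will produce false factors.** A reader might infer that unstated cuts will be picked with the outcome in view and quote the 32 to 34% error rate. The article does not say so, and one cut fixed in advance keeps the error near 5%.
- **That the Cox model will hold coarse, grouped terms.** The article does not say in what form a selected variable enters that model.
- **That the trial's main comparison is compromised.** The univariate step is described as exploratory, and the unadjusted comparisons do not pass through it.

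**Conclusion.** The point holds in limited form. The article names a univariate method that cannot handle continuous factors without grouping, and uses its result to choose the adjustment variables. For a continuous, roughly normal factor of moderate strength, a prespecified median split would lower the chance of passing the screen by about 13 to 20 percentage points.

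The size rests on assumptions that the documents do not supply: the log hazard ratios, normality, a log-linear effect, exponential times and the censoring fraction. It also applies only if at least one continuous factor is screened, which is plausible in this population but not stated. The weakness is modest and worth correcting.

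**What to change.** Replace the Kaplan–Meier sentence in section 3.7 with:

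> Univariable associations with time-to-event outcomes will be estimated with Cox models, with continuous variables kept on their own scale there and in the multivariable model; Kaplan–Meier curves will be used for the randomised arms and factors that are categorical by nature.

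The cost is one sentence. Cox regression is already planned, and the change needs no data beyond the factors the screen would use anyway. The small downside is that a linear log-hazard is assumed, which can be checked with a quadratic or spline term. The change leaves the P < .05 screen in place; adjusting instead for prespecified covariates in continuous form would remove the dependence on the screen altogether, but that is a separate decision.

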#### Inclusion criteria

2.7.1

Only patients who meet the following criteria will be included:

(1)Age ≥18 years.(2)Fulfillment of the diagnostic criteria of acute exacerbation of chronic obstructive pulmonary disease, acute respiratory distress syndrome, or postoperative respiratory failure requiring mechanical ventilation for ≥24 hours.(3)Clear consciousness and the ability to act in accordance with instructions.(4)Stable cardiopulmonary functions.(5)Voluntarily participation after signing an informed consent.

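### The Cox model's variables are chosen by a univariate P < .05 screen on the trial's own outcomes, and the randomised arm is not exempted from it

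*Protocol article*

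**What the plan says.** Section 3.7 (Statistical analysis) sets a two-step rule. In the first step the Kaplan–Meier method "will be used for univariate analysis to explore each possible related factor". In the second, "The multivariate Cox model will be used to adjust for variables with statistical significance", where significance means P < .05 in the first step. The model's stated aim is to show how those variables affect the outcomes; a treatment effect is not mentioned. The candidate factors are not named, and the arm is neither listed among them nor declared a permanent term.

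The other methods in section 3.7 are a paired t-test for change within a group, chi-square for counts and a rank sum test for graded data. Mechanical ventilation time (3.2.2) and length of ICU stay (3.2.3) are durations. As the methods are listed, Kaplan–Meier and Cox are the only ones that could compare the two arms on them.

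The population is mixed. Section 2.7.1 requires "Fulfillment of the diagnostic criteria of acute exacerbation of chronic obstructive pulmonary disease, acute respiratory distress syndrome, or postoperative respiratory failure", with ventilation for at least 24 hours. Table 1 fixes recruitment by centre at 80, 40 and 40 patients. APACHE II appears in the exclusion criteria (2.7.2).

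**The concern.** Univariate screening followed by a multivariable model is a way of searching for prognostic factors in a cohort. In a randomised trial the question is the effect of the arm, and the adjustment set should be settled before outcomes are seen. Section 3.7 leaves two things open.

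- **Whether the arm is screened.** If it is, an adjusted treatment effect exists only when the unadjusted one is already significant. Power then cannot exceed that of the unadjusted test, and the estimates that survive are selected for being large.
- **Which hazard ratio is estimated.** Hazard ratios are non-collapsible: the treatment hazard ratio changes with the covariates in the model even when randomisation balances them. If the covariates are picked by their P values, the quantity being estimated is not known until the outcomes are in.

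Diagnosis group is an obvious candidate covariate here, yet it enters only if it happens to reach P < .05.

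**Working it through.** **The plan's own figure.** Section 2.4 gives "The test level was α = 0.05", "The test efficiency was 1 - β = 0.80" and "the effect size was set as d = 0.50". The normal approximation is n = 2(1.960 + 0.842)²/0.50² = 62.8, so 63 per group. The exact two-sided t-test gives power 0.7952 at 63 and 0.8015 at 64, so 64 per group. This matches "the number of participants needed in each group was 64, totaling to 128 participants". Sidedness is not stated, but a one-sided test would need 50 and does not fit. Then 128/(1 − 0.20) = 160, which matches "Considering an attrition rate of ≤20%, the total number of participants required for this study was calculated to be 160". The sample size reproduces, but it rests on a standardised difference. The documents give no hazard ratio, event count, covariate strength or censoring rate.

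**Simulation inputs.** N = 128 comes from section 2.4. All else is assumed: hazard ratio 1.65 (log 0.50) or 1.0; 20% of patients censored at a common cut-off; five or six independent normal covariates, three of them prognostic. There were 2,000 trials per scenario, with Wald tests at two-sided 0.05. The Monte Carlo standard error is √(0.05 × 0.95/2000) ≈ 0.005 near 0.05 and √(0.7 × 0.3/2000) ≈ 0.010 near 0.70.

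Covariate log hazard ratios per SD: A = 0.3, 0.3, 0.3, 0, 0; B = 0.5, 0.5, 0.2, 0, 0; C = 0.7, 0.5, 0.2, 0, 0, 0.

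Rejection rate for the arm:

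| True HR | Scenario | Arm alone | Pre-specified covariates | Arm kept, covariates screened | Arm also screened |
|---|---|---|---|---|---|
| 1.65 | A | 0.596 | 0.702 | 0.674 | 0.548 |
| 1.65 | B | 0.511 | 0.697 | 0.688 | 0.477 |
| 1.65 | C | 0.438 | 0.696 | 0.691 | 0.402 |
| 1.0 | A | 0.056 | 0.065 | 0.062 | 0.032 |
| 1.0 | B | 0.044 | 0.051 | 0.046 | 0.020 |
| 1.0 | C | 0.050 | 0.062 | 0.052 | 0.018 |

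**If the arm is screened** (true HR 1.65):
- The arm is dropped in 0.404, 0.489 and 0.561 of trials.
- Power lost against the pre-specified model is 0.702 − 0.548 = 0.154, 0.697 − 0.477 = 0.220 and 0.696 − 0.402 = 0.294.
- When the arm is kept, its mean log HR is 0.605, 0.640 and 0.631. The pre-specified model averages 0.520–0.526, so only a small part of the excess over 0.50 is ordinary small-sample bias.

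**If the arm is always kept:**
- Power lost is 0.028, 0.009 and 0.005.
- Under the null, the rejection rate is no higher than for the pre-specified model in any scenario.

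**Dependence of the hazard ratio on the adjustment set.** The same simulated trials give a mean log HR of 0.435, 0.399 and 0.364 with the arm alone, against 0.520, 0.526 and 0.522 with all covariates. On the HR scale, scenario C moves from exp(0.364) = 1.44 to exp(0.522) = 1.69.

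**A second set of assumptions.** With 160 patients, HR 1.5, a severity score at log HR 0.5 per SD, diagnosis effects of 0 and ±0.4, censoring at day 28 and 1,500 runs, power was 0.507 for the arm alone, 0.689 pre-specified and 0.467 with the arm also screened. The null rejection rates were 0.050, 0.052 and 0.020. The direction is the same; this run did not include the reading in which the arm is always kept.

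**The case against.** A reader might infer that the plan does screen the randomised arm. The text does not establish this. It exempts nothing from the screen, but adjusting for a set of variables normally means adding them around a retained exposure. On that reading the power loss nearly vanishes, because screening picks up the strong covariates anyway. This part of the objection stands, and the 15–29 point loss must be presented as belonging to one reading only.

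A reader might also infer that false positives are inflated. Neither simulation supports that: the rule is conservative if the arm is screened and shows no visible inflation if it is kept.

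It can be said, too, that section 3.7 never calls the Cox model the primary treatment comparison and describes the first step as exploration, so this may be only a side search for prognostic factors. That is possible, but the section names no other between-arm method for the durations.

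Finally, covariate lists are often left to a statistical analysis plan. That would answer a complaint that the list is missing. It does not answer this one, because the article states a selection rule and the rule is a poor one. The point that APACHE II may not be stored as a baseline value is fair: it appears only within an exclusion criterion, and the assessment schedule (Figure 2) is not shown.

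**Conclusion.** The concern holds in a limited form. Section 3.7 selects Cox variables from the trial's own outcomes at P < .05 and does not say that the arm is always in the model.

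- If the arm is screened, it is lost in about 40–56% of trials at an assumed HR of 1.65, power is about 0.40–0.55 instead of 0.70, and the surviving log HR averages 0.61–0.64 against 0.50.
- If the arm is kept, the cost is 0–3 points of power. The remaining defect is that the adjustment set, and with it the conditional hazard ratio, is not fixed in advance.

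The sizes rest on assumed hazard ratios, covariate strengths and censoring, and on independent normal covariates rather than the trial's own diagnosis groups and centres. The need to fix the model in advance does not rest on them.

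**What to change.** Replace the screening rule, before outcome data are examined, with one model for the time-to-event outcomes. Suggested wording:

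> Ventilation time and length of ICU stay will each be analysed with a Cox model that always includes the randomised arm, is adjusted for diagnosis group (AECOPD, ARDS, postoperative respiratory failure) and baseline APACHE II score, and is stratified by centre. No variable will be selected by its P value. The treatment hazard ratio and its 95% confidence interval will be reported whatever the P value. Any search for other prognostic factors is exploratory.

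Confirm first that APACHE II is recorded as a baseline value; if it is not, omit it or name another baseline severity measure that is.

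The cost is small. The covariate list must be written down in advance, and the model spends three degrees of freedom beyond the arm (two for diagnosis group, one for APACHE II). The sample size stays at 64 evaluable per group and 160 in total.

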#### Incidence of ICU mechanical ventilation complications

3.2.1

The ICU consciousness disorder assessment form and delirium scale analysis system will be used to evaluate each patient state of consciousness. The presence of ICU-AW will be judged according to the British Medical Research Council grade 6. The incidence of ventilator-associated pneumonia, pulmonary infarction, and pressure ulcers will also be observed.

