#### Mechanical ventilation time

3.2.2

Data will be obtained to determine whether the mechanical ventilation time in ICU is shortened during the period from admission to the end of the trial.

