#### Length of ICU stay

3.2.3

The period from admission to discharge from the ICU will be recorded.

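### The only multivariable model named, a Cox model, is aimed at the study outcomes without being limited to the two durations, and it does not fit complications or cost as the protocol defines them

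*Protocol article*

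**What the plan says.** Section 3.2 has four outcome headings.

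- Complications (3.2.1): state of consciousness and delirium by scale, presence of ICU-acquired weakness by muscle grading, and three further events: "The incidence of ventilator-associated pneumonia, pulmonary infarction, and pressure ulcers will also be observed". No time to onset is part of the definition.
- Ventilation time (3.2.2): "whether the mechanical ventilation time in ICU is shortened during the period from admission to the end of the trial".
- ICU stay (3.2.3): "The period from admission to discharge from the ICU will be recorded".
- Cost (3.2.4): "Hospitalization expenses from admission to discharge from the ICU will be recorded".

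Section 3.7 gives the unadjusted tests by data type, including "The chi-square test will be used for the counting data and the rank sum test will be used for grade data". It then adds an exploratory step, "The Kaplan–Meier method will be used for univariate analysis to explore each possible related factor", and a multivariable step, "The multivariate Cox model will be used to adjust for variables with statistical significance". The purpose of that last step is "to detect the influence of these variables on the study measure outcomes". No logistic, linear or other regression model is named.

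Section 3.5 says that the time of occurrence of each adverse event is recorded.

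**The concern.** A Cox model needs a time and an event or censoring indicator for every patient. Two of the four outcomes (ventilation time, ICU stay) can supply these. The other two, as defined, do not. Section 3.7 treats complications as yes/no data in the unadjusted analysis, yet the only adjusted model it offers requires an event time.

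This touches a central outcome. Complications come first in section 3.2, and the sample size rationale in section 2.4 refers to preventing and treating complications and adverse outcomes.

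The risk is that an analyst who follows the sentence literally has to invent a time axis. The per-patient durations that section 3.2 provides are ventilation time and ICU stay, and the introduction expects the intervention to shorten ventilation. If ICU stay became the time for a yes/no complication, a benefit on stay would reappear as apparent harm on complications. For cost, the output would be a hazard ratio on a money scale.

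**Working it through.** The protocol states no figure for the Cox analysis, so there is none to reproduce. The check sets each outcome against the model and then sizes the effect under assumptions.

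**1. Fit of model to outcome**

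| Outcome | As defined in 3.2 | Unadjusted method in 3.7 | Suits Cox as defined? |
|---|---|---|---|
| Complications | presence or incidence | chi-square | no, time not defined |
| Ventilation time | duration | not tied to a named outcome | yes, once event and censoring are set |
| ICU stay | duration | not tied to a named outcome | yes, once event and censoring are set |
| Cost | money | not tied to a named outcome | no |

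**2. Complications with ICU stay as the time axis**

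Let *p* be the probability of a complication in an arm, independent of stay, and *h(t)* the hazard of leaving the ICU on day *t*. With stay as the time and complication yes/no as the event, the event hazard is *p × h(t)*. The ratio between arms is

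(*p*₁ × *h*₁(t)) / (*p*₀ × *h*₀(t)).

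If *p*₁ = *p*₀, the incidence cancels and what remains is *h*₁(t)/*h*₀(t), the discharge hazard ratio. The model then reports the effect on stay under the label of a complication effect.

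Inputs: 80 per arm (section 2.5, Table 1) and P < .05 (section 3.7). The rest is assumed: equal incidence in both arms, lognormal stay with median 10 days and log-SD 0.7, and a Cox model with arm as the only covariate. There were 4,000 simulated trials per scenario.

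| Stay shorter by | Mean HR | P < .05 at 30% incidence | P < .05 at 50% incidence |
|---|---|---|---|
| 10% | 1.15–1.16 | 8–9% (both incidences) | 8–9% (both incidences) |
| 20% | about 1.35 | 17% | 25% |
| 30% | 1.61 | 36% | 54% |

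The chi-square test on the same data rejected in about 4–6% of trials throughout. A separate run with other assumptions (mean stay 10 against 14 days, 40% risk in both arms) gave a hazard ratio of about 1.98 and 73% rejection.

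**3. Complications with onset dates as the time axis**

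Same lognormal stay, 20% shorter, 30% and 50% incidence, 2,000 trials per cell. Patients without the complication are censored at ICU discharge.

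- Onset uniform over the stay: HR 1.16–1.18, rejection 8–12%.
- Onset mostly early: HR about 1.08, rejection 5–7%.
- Complication also prolongs stay by 50–100%: HR 1.08–1.28, rejection 5–17%.

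**4. Complications with one constant time for everyone**

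With assumed risks of 30% and 50%, the true risk ratio is 0.30/0.50 = 0.60. Cox gave about 0.59, with a mean standard error of 0.26 against an empirical SD of 0.22. That is close to the risk ratio and conservative.

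**5. Cost**

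With lognormal cost, log-SD 0.6 in both arms and a true cost ratio of 0.80, Cox on the cost axis gave a hazard ratio of about 1.40. It exceeds 1 because lower cost counts as an earlier event, and it is neither the ratio 0.80 nor a sum of money. In separate runs with equal mean costs, the error rate stayed near 6%. The loss for cost is therefore one of interpretation.

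**The case against.** The strongest reply is that section 3.7 proceeds by data type. Kaplan–Meier precedes Cox and is itself a time-to-event method, and complications already have the chi-square test. On that reading, Cox was meant only for ventilation time and ICU stay, and every sentence has a sensible role. The word "all" does not appear, so a reader who infers that Cox is expressly assigned to every outcome goes further than the text. This stands as a plausible account of intent. It does not remove the point: the sentence carries no such limit, and if the limit is read in, complications and cost are left with no adjusted model.

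Second, a reader might infer that complications have no event time at all. The protocol does not support that. Section 3.5 records when adverse events occur, so time to first complication could be built for some events. Section 3.2.1 does not ask for it, however, and delirium and ICU-acquired weakness are found by assessment, so their onset is at best an assessment date.

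Third, nothing says that ICU stay would be the Cox time. The 1.35 figure comes from the worst of the axes tried, and onset dates reduce it considerably.

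Fourth, section 3.7 uses the Cox step to study related factors. It does not say that treatment arm is in the model. The simulations put arm alone in the model, so they show what can happen to a treatment estimate, not what the protocol says will be reported.

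Finally, event and censoring definitions are commonly left to an analysis plan, and their absence from a condensed article is not criticised here. The point concerns a method and a target that the article does state and that do not match.

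**Conclusion.** The point holds in a limited form. Section 3.7 names Cox as its only multivariable model and directs it at the study outcomes without restriction, and two of the four outcomes are not times to event as defined.

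For complications, the size depends on the unstated time axis: at a 20% shorter stay, from about 1.08 with 5–7% false rejection (mostly early onset) to about 1.35 with 17–25% (ICU stay as the time). Stay lengths, incidences, onset patterns and the size of the reduction are all assumptions. For cost, the effect is that the result cannot be stated as a saving.

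It would be tempting to conclude that the adjusted results will be wrong or uninterpretable. The protocol does not support that: with a constant time Cox comes close to a risk ratio, with onset dates the distortion is modest, and for cost the error rate is near nominal. The unadjusted chi-square comparisons of complications are unaffected. This is a mismatch that should be corrected before analysis. It does not invalidate the trial's main comparisons.

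**What to change.** In section 3.7:

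- restrict Kaplan–Meier and Cox to ventilation time and ICU stay;
- for each complication, use logistic regression, or modified Poisson regression if a risk ratio is wanted, with arm and the same covariates;
- for cost, use a gamma model with log link, or a linear model with robust standard errors, and report the adjusted difference in money.

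This takes one or two sentences and needs no new data and no more patients. The small downside is three model types to report in place of one.
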